## Abstract

**Abstract:**

**Introduction:**

Psychotic disorders account for significant morbidity and healthcare costs and yet their pathophysiology remains poorly understood. The National Institute for Health and Care Research (NIHR) Severe Mental Illness Longitudinal Evaluation (SMILE) BioResource is a collaborative project that aims to collect clinical data and biological samples from people with psychosis for long-term storage, future projects and recontact for targeted trials.

**Methods and analysis:**

The NIHR SMILE BioResource cohort will initially include up to 2000 UK-based patients with a recorded diagnosis of psychosis. Clinical symptoms will be captured using self-report and clinician ratings. Biosamples will enable genotyping and wider omics as further funding allows. Study data will be analysed to facilitate development of discovery science for underlying mechanisms of psychotic disorders and recall of participants for targeted interventional studies.

**Ethics and dissemination:**

This study is sponsored by the University of Oxford and received full ethical approval from Wales REC 2. SMILE BioResource biosamples and data will be stored long-term by the NIHR BioResource. Researchers who are interested in applying to use these biosamples and data, and/or recontacting SMILE participants can find further information on the website of the NIHR BioResource.

STRENGTHS AND LIMITATIONS OF THIS STUDYA multifaceted understanding of mental health, for example, biological, cognitive and sociodemographic factors.Provides possibilities for co-consent to research studies with a similar design.Currently only recruits participants who have capacity to consent, which may lead to selection bias.Challenges ensuring people from all sections of society, irrespective of ethnic or socio-economic background, are represented in this resource.^23^

## Introduction

 Psychotic disorders, including schizophrenia, schizoaffective disorder and affective psychosis, impact up to 3% of the population and can severely affect quality of life for individuals and their families, including the ability to function socially and professionally. People with psychotic disorders also die around 15 years earlier than the general population, largely due to cardiometabolic disease.^1 2^ Despite current best treatments, psychotic disorders represent a significant and unaddressed need. Individuals living with psychotic disorders represent a patient group whose illness has not received the research investment or potential equal to its personal, family and societal burden.

There is considerable diagnostic heterogeneity in psychotic disorders; herein, we use the terms severe mental illness (SMI) and ‘psychosis’ to encompass schizophrenia, schizoaffective disorder, affective and broader defined primary psychotic disorders, as defined by International Classification of Diseases (ICD)-11 (see Methods and analysis section).

Studies have reported different pathological factors that contribute to psychosis including genetic risk, subcortical dopamine and glutamatergic dysfunction, structural and functional grey and white matter changes, and cognitive impairment impacting executive function, attention and working memory.^3^,^5^ This better understanding of pathological processes may eventually lead to more specific and effective therapies, yet progress is slow. While considerable efforts have elucidated pathophysiological processes that also reflect the illness’ heterogeneity, there are no biomarkers used in clinical practice to aid diagnosis or to guide treatment. This may be due to the scale of the challenge. Scalable and accurate study design, alongside representative, replicable and robust testing of accurate biomarkers is necessary to advance understanding of the complexity of psychosis and its clinical application.^6^

Given the need for scale and replication, blood, plasma and serum may offer accessible samples for biomarker identification, with potential to improve clinical care for people who experience psychosis and to better target interventional studies and drug trials.^6^ The Severe Mental Illness Longitudinal Evaluation (SMILE) BioResource is designed to address the gap in long-term storage of biological samples and phenotypic data to support future discovery science involving people with psychosis.

A bioresource is a collection of biological samples and clinical data from consented individuals with possibilities for follow-up contact. ‘Biorepository’ and ‘biobank’ are other names used to describe a facility that receives, processes, stores and manages access to biological samples.^7^ The primary aims of a bioresource are to archive and distribute collected samples and data to support scientific research.^7^ Collected samples are quality-controlled and can be processed for serum or plasma, frozen, and stored for genomic, proteomic, metabolomic, inflammatory and other testing. Samples can then be requested for research by biomarker or phenotype.^8^ Quality control and standard operating procedures for sample collection and handling are essential across large, multisite resources to minimise avoidable heterogeneity and confounds.

The SMILE BioResource is funded by the National Institute for Health and Care Research (NIHR) Mental Health Translational Research Collaboration Mission; it is a collaborative project involving researchers at the University of Oxford, the University of Birmingham, Cardiff University, King’s College London and the national NIHR BioResource. The SMILE BioResource will collect relevant information for understanding how biological (eg, genomic, proteomic, inflammatory) and environmental factors influence psychosis presentation, symptom profile, prognosis and treatment response. The SMILE BioResource will provide a recontactable cohort with stored biosamples for recall to future studies, including trials and observational studies. A bioresource with extensive mental health data and biosamples offers significant potential for research into psychosis for many years to come.

## Methods and analysis

### Design

All collected data and samples will be transferred to the NIHR BioResource for long-term storage by the end of January 2028. The NIHR BioResource is a research tissue bank that provides researchers with access to a large panel of consented volunteers, along with their genetic, health and lifestyle data and stored samples. The NIHR BioResource comprises a collection of over 300 000 recallable volunteers, including individuals with rare and common illnesses as well as individuals from the general population. The unique contribution of the SMILE BioResource will be a focus specifically on people with psychosis to ensure they are represented within this established and robust resource.

Beginning recruitment in November 2025, the SMILE BioResource is funded to recruit 2000 individuals with a recorded diagnosis that meets criteria for psychosis as defined by ICD-11, including 6A20 (schizophrenia), 6A21 (schizoaffective disorder), 6A22 (schizotypal disorder), 6A23 (acute and transient psychotic disorder), 6A24 (delusional disorder), 6A25 (symptomatic manifestations of primary psychotic disorders), 6A2Y (other specified primary psychotic disorder) and 6A2Z (schizophrenia or other primary psychotic disorders, unspecified).

While some definitions of SMI also include bipolar disorder and major depressive disorder, these cohorts are being collected as part of the Genetic Links to Anxiety and Depression NIHR Bioresource study. SMILE will focus on SMI within the scope of psychosis. UK primary care data reported an incidence of 9.2 per 100 000 for schizophrenia and 22.3 per 100 000 person years for other psychotic disorders compared with 15.0 per 100 000 person years for bipolar disorder.^9^ This indicates that within incident cases of psychosis, schizophrenia and non-schizophrenia psychoses make up the largest proportion of potential SMI diagnoses currently underserved within national Bioresource infrastructure.

#### Informed consent

Informed consent will be obtained prior to any research procedures. To join the SMILE BioResource, patients must consent to:

Provide a biological sample and data at the study visit.‘Access in principle’ to their electronic health records and other relevant records.Their data and biosample being stored long-term by the NIHR BioResource.Their de-identified data being used for research approved by the NIHR BioResource.Be invited to future research for which they may be eligible.

Where study sites have trials or cohort studies also recruiting participants with SMI, these participants may also be presented with information about co-consenting to the SMILE BioResource.

People with SMI may have difficulty with insight, memory and cognition which makes research participation more challenging. However, capacity to consent to research, as with any capacity decision, is context dependent and specific to a particular question or setting. Participants may have positive symptoms but may retain capacity to make a decision about study participation. All research staff who recruit to the SMILE BioResource are trained in good clinical practice and work with clinical teams to ensure that support is in place for communicating study information to potential participants. Some patients may be too unwell to provide consent to participate in SMILE, for example during an acute episode; these patients can instead be approached later in their illness course once they have recovered.

Based on population descriptives, we estimate there will be ∼5% of patients with severe, intractable treatment resistance that affects capacity to join research longer term.^10^ We will monitor recruitment figures, Positive and Negative Syndrome Scale (PANSS) and Clinical Global Impression-Schizophrenia (CGI-S) scores, and we will assess our data against representative cohorts with the most severe illness scores from published data. We will consider adding a modification to include consultee opinion in keeping with Health Research Authority guidance.

### The study visit

Each study visit will last between 30 minutes and 60 minutes and will be conducted by a trained clinical researcher. Participants will be able to bring a close relative, friend, care coordinator or peer support worker to the study visit. Participants will be offered a £25 shopping voucher to thank them for their participation.

### Research questions

The first stage of the SMILE BioResource will involve the collection of biosamples and data at study sites as well as analysis by SMILE study investigators. Our initial primary research aim are:

To establish the prevalence of cognitive difficulties and physical comorbidity and their association with length of illness and sociodemographic factors.

Multivariate methods will be employed to characterise association between independent variables (eg, length of illness, sociodemographic factors) and dependent variables (eg, cognitive performance, physical health symptoms).

To establish the influence of biological risk factors, for example, genomic risk on time and severity of physical health comorbidity and cognitive decline.

Similarly to our first objective, a multivariate approach will be employed to characterise the association between biological risk factors (eg, robust polygenic risk scores) and (1) cognitive (2) physical health outcomes.

The second stage of the SMILE BioResource will involve long-term storage of all study data and biosamples as well as the opportunity for academic and industry researchers to apply to the NIHR BioResource to use these data and biosamples for research and/or to invite SMILE BioResource participants to future research.

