### Outcome measures

Biosample (blood or saliva sample).Up to 50 mL of blood may be taken from a participant at one point in time only. Blood samples will be collected using blood collection tubes (eg, vacutainer; 2× EDTA and 1× serum tube). Where possible, blood taking is synchronised to the morning and when samples are being taken for standard clinical care. Blood samples must be sent on the same day as collected to the UK Biocentre (where the NIHR BioResource stores research samples). Extracted DNA will be stored in −80°c freezers with careful temperature logging and monitoring.Self-collection saliva kits will be used to collect saliva samples if it is not possible to collect blood. DNA from saliva can be used for most genetic analysis but not for whole-genome sequencing.Patient-reported outcome measures (PROMs).PROMs will be collected to capture a patient’s experiences and perspectives on their health and treatment. PROMs include the Altman self-rating mania scale^11^; the Bespoke Adapted Chemical Use, Abuse and Dependence Scale for Alcohol and Drug Use^12^; a Child Trauma Screen^13^; a Generalised Anxiety Disorder Assessment^14^; the Patient Health Questionnaire^15^ and a Health and Lifestyle Questionnaire developed by the NIHR BioResource.Clinician-reported outcome measures (CROMs).CROMs will be completed by a trained clinical researcher. They are important to assess and report on a patient’s health status, illness severity and functional abilities. The CROMs that we will use include the CGI-S scale^16^; the PANSS 6-item^17^; and the functional remission of general schizophrenia.^18^Clinical data, including vital signs (systolic and diastolic blood pressure and pulse rate); full blood count and differential, biochemistry, lipids and glucose; C-reactive protein; ECG; regular medication; and physical health diagnoses will all be obtained from patient health records.Demographic information.Date of birth, sex at birth and gender, area postcode for deprivation indices and ethnicity, as recorded by the 2021 UK census ethnicity classification.Cognition.The digital Symbol-Symbol Substitution Task (SSST) is an alternative version of the digit-symbol substitution task (DSST), which is a well-established psychometric test paradigm used to measure various aspects of cognition, including psychomotor speed, attention and visuospatial function.^19^ The SSST shows high correlation with the standard DSST (r=0.8) and is being used in multiple patient populations, including those with schizophrenia and other psychotic disorders.^20^,^22^ For the SSST, participants are asked to match a symbol to another symbol according to pre-existing pairs. We will collect data for the SSST using a computing device (eg, laptop, tablet) that will record the number of correct and incorrect responses within 90 seconds.Relevant information from care notes including recent or current hospitalisation, home treatment episodes, medication prescription (including current drug, dosing, frequency and compliance) and recent changes, and new mental health or physical health diagnoses.Permission to access the participant’s electronic health records and other records (‘access in principle’) that may be relevant for research.‘Access in principle’ means that for future studies, only records that are strictly relevant for approved research purposes will be accessed. At the point of data collection, only medical records that are strictly relevant to the study of SMI are collected as CROMs, for example, information about regular medications and blood results.

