### Participant recontact

The NIHR BioResource will manage any recontact with SMILE BioResource participants for the purpose of inviting them to take part in further research studies, including clinical trials, or to donate fresh samples for additional analysis. Recontact is currently available and scheduled until current funding expires in January 2038. However, our vision is one of a long-term and growing resource.

Follow-up studies may involve clinic visits, telephone assessments or home visits by study staff. The maximum number of invitations to studies involving face-to-face recall is approved to be four in every 12-month period. Within this same 12-month period, participants may be invited to up to four further online-only studies (eg, questionnaires or cognitive test-based studies) that they can complete in their own time.

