## Discussion

To date, there has been a paucity of well-characterised, openly available resources for targeted biomarker investigation involving individuals with psychosis. Such resources are needed given that scientific discovery, assay development and technological advances are occurring at pace. It is likely that current treatment efficacy is diminished by an inability to stratify patients into subtypes based on biomarkers (such as genomic, inflammatory or metabolic subtypes) and to deliver tailored treatment pathways that address individual disease processes. Furthermore, reliance on cross-sectional data has limited investigation into biomarkers and their relation to disease trajectory. The implementation of screening programmes and timely preventative interventions remains a challenge.

The SMILE BioResource will offer an invaluable resource, developed with patients, to help address these unmet needs. Through longitudinal, in-depth phenotyping of a large patient cohort with a history of SMI and psychotic disorder, together with stored samples, the SMILE BioResource will provide a wealth of clinical and biological data that reflects the heterogenous and dynamic nature of this mental illness. The SMILE BioResource could help to advance understanding of the relationship between biological and environmental risk factors and their influence on psychosis presentation, symptom profiles, prognosis and response to treatment.

By aligning with the core missions of the NIHR Mental Health Translational Research Collaboration and the NIHR Bioresource, SMILE will provide a key substrate for multiomics and next-generation sequencing technologies, enabling investigation into the underlying biology of psychosis. Ultimately, the SMILE BioResource will facilitate early-stage translational research into novel drug targets and innovative therapies to improve clinical practice and mental health through discovery medicine.

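### Aim 2 targets cognitive decline, but the article describes one cognitive test at one visit, so the stated analysis cannot separate lower level from faster decline

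*Protocol article*

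**What the plan says.** Under Research questions, the article lists two initial primary aims. The second is "To establish the influence of biological risk factors, for example, genomic risk on time and severity of physical health comorbidity and cognitive decline". Both belong to the first stage, which the study's own investigators analyse: "The first stage of the SMILE BioResource will involve the collection of biosamples and data at study sites as well as analysis by SMILE study". The analysis given for the second aim, with cognition and physical health as the outcomes, is that "a multivariate approach will be employed to characterise the association between biological risk factors (eg, robust polygenic risk scores) and (1) cognitive (2) physical health"; it is introduced as similar to the approach for the first aim.

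The data for this are described in three places:

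- **Informed consent:** participants agree to "Provide a biological sample and data at the study visit", with the visit in the singular.
- **The study visit:** "Each study visit will last between 30 minutes and 60 minutes and will be conducted by a trained clinical researcher". This gives a length for the visit but no second time point or interval.
- **Outcome measures:** the only cognitive test is the SSST, on a device "that will record the number of correct and incorrect responses within 90 seconds". No repeat and no premorbid estimate is described.

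The Discussion presents the resource as working "Through longitudinal, in-depth phenotyping of a large patient cohort with a history of SMI and psychotic disorder".

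**The concern.** The aim and its own analysis sentence name different targets. The aim speaks of decline, which needs at least two measurements per person or a credible earlier reference value. The analysis sentence speaks of cognitive outcomes, and the data described give one score per person. An association between a polygenic score and that single score could reflect ability that was lower before onset, faster loss since onset, or both.

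What is at stake is the conclusion that can be drawn. A finding about level could be taken as an answer to the stated aim about decline. Researchers who later apply for the data could also expect repeated cognitive scores that nobody is scheduled to collect.

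**Working it through.** The article gives no power, sample size or effect-size figure for this aim, so there is no figure to reproduce. The check has two parts.

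**1. Is there a second cognitive score anywhere?** There are three candidate sources.

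- *The visit schedule.* One visit is described. The explicit limit to a single point in time, in Outcome measures, applies to blood. That cognition is tested once is therefore an inference from the single visit and the absence of any repeat.
- *Health records.* Access in principle is defined for future studies. Nothing says that records hold SSST scores.
- *Recontact.* Under Participant recontact, "participants may be invited to up to four further online-only studies (eg, questionnaires or cognitive test-based studies"). These are optional invitations managed by the NIHR BioResource, not a scheduled repeat of the SSST and not part of the first-stage analysis.

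None of the three supplies a planned second score.

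**2. What can one score per person show?** Write the score of participant i as

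y_i = a + β·g_i + (γ + δ·g_i)·d_i + e_i

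where g is the standardised risk score, d is length of illness, β is the effect of risk on level, γ is the average change per year, and δ is the effect of risk on yearly change. Aim 2 is about δ. If g is independent of d, a regression of y on g and d estimates, for g,

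β + δ·E[d].

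Level and decline enter as one sum.

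Inputs: N = 2000 (Design section). The rest are assumptions: d uniform on 0 to 30 years, so E[d] = 15; γ = -0.01 SD per year; residual SD 1; 500 simulated cohorts.

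| Scenario | β | δ per year | Expected: β + 15δ | Simulated mean (SD) |
|---|---|---|---|---|
| Risk lowers level only | -0.15 | 0 | -0.15 | -0.149 (0.023) |
| Risk steepens decline only | 0 | -0.01 | 15 × -0.01 = -0.15 | -0.151 (0.023) |

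The effect sizes were chosen so that the two sums agree. The point does not depend on that choice: for any level effect there is a decline effect that gives the same coefficient. The decline-only δ that mimics a level effect of -0.15 SD is -0.15/E[d]:

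| Assumed mean length of illness (years) | δ (SD per year) |
|---|---|
| 5 | -0.030 |
| 10 | -0.015 |
| 15 | -0.010 |
| 20 | -0.0075 |

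**Could an interaction rescue it?** Adding g × d to the same simulation separated the scenarios: the mean interaction was -0.0001 SD per year (SD 0.0025) for level only and -0.0098 (SD 0.0027) for decline only. This works because β was made the same at every length of illness. If cohort, survival or selection effects make it β + κ·d, the interaction estimates δ + κ, and one cross-section cannot split that sum. The article does not specify this interaction, and it would remain a contrast between people.

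**The case against.** The strongest reply is that the planned analysis is modest. Its sentence names cognitive outcomes, not change, so the mismatch comes down to one phrase in the aim. This is also a condensed article, and a fuller protocol or analysis plan may say more. Part of this stands: the repair is mainly wording, and nothing in the text says that results will be labelled as decline. But no analysis model recovers within-person change from one score per person, so if a repeat exists elsewhere, the article should say so.

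A reader might also infer stronger conclusions that the article does not support:

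- *That Aim 2 as a whole cannot be answered.* The aim also covers time and severity of physical comorbidity. Outcome measures says that physical health diagnoses come from health records, which can supply dated events. That part stands, and nothing in this argument requires restricting it to events after the visit. Doing so would discard usable earlier diagnoses.
- *That the longitudinal claim in the Discussion is simply false.* The sentence describes the whole resource, which includes record access and recontact scheduled to January 2038. It is too broad for cognition, not wrong throughout.
- *That length-of-illness slopes will be passed off as decline.* Length of illness belongs to the first aim, which claims only association and names cognitive performance. The article specifies no age-adjusted model from which a false decline could be calculated.

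**Conclusion.** The point holds for cognition only. Within-person cognitive decline is a stated first-stage target that the described data cannot deliver, and the stated association cannot tell it from a difference in level: about -0.15 SD per SD of risk score in both simulated cases. The size of that coefficient rests on assumed effects and an assumed spread of illness length. The failure to identify decline rests on neither, only on there being one score per person. That premise is inferred from the single visit and the lack of any described repeat, and is the natural reading of the article.

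**What to change.** 1. In Aim 2, replace cognitive decline with *cognitive performance (SSST) at the study visit*. Leave the part on physical comorbidity as it is.
2. Add one sentence to the analysis description: *associations of SSST score with risk scores or length of illness will not be interpreted as within-person decline*.
3. In the Discussion, state that longitudinal refers to linked health records and possible recontact, not to scheduled cognitive assessment.

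These are wording changes with no effect on recruitment or data collection.

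If decline is to remain an aim, specify a repeat SSST, its interval and a model for change. This costs more. Recontact runs through the NIHR BioResource as invitations to further studies, so attrition has to be planned for. A self-completed online repeat would also differ in mode from the researcher-conducted visit, and practice effects would be mixed with true change; the plan should say how both are handled. This option is not needed to repair the aim.
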